#### Exclusion criteria

The exclusion criteria include the following: (1) history of knee surgery or waiting for knee surgery (e.g., knee replacement or arthroscopy); (2) history of knee injection in the past 6 months or arthroscopy in the past 12 months; (3) knee pain caused by other diseases (e.g., trauma, fracture, gouty arthritis, infection, malignant tumor); (4) psychiatric or neurological disorders (e.g., traumatic brain injury, stroke, Parkinson’s disease); (5) coagulation disorders, severe acute or chronic organic disease; (6) MRI contraindications (e.g., claustrophobia, cardiac pacemaker or other metallic agents embedded within body); (7) severe skull anatomical asymmetry or definite lesions found on magnetic resonance scanning; (8) alcohol or drug abuse; (9) pregnant or lactating or planning a pregnancy; and (10) recent acupuncture in 1 month.

During the trial period, patients with KOA who meet the following criteria will be excluded from the study: (1) protocol violation such as taking analgesic without permission or receiving additional treatment that may interfere with the efficacy of acupuncture, (2) withdrawal of consent for study participation because the patients do not wish to continue, (3) missing more than 6 of 24 acupuncture treatment sessions, and (4) occurrence of a serious adverse event that the doctors consider should lead to termination of trial participation.

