### Sample size

Since this is a pilot study, a formal sample size calculation is not performed [27]. According to fMRI studies, a sample size of 20 subjects are sufficient to detect a significant difference with a type I error of 5%, and about 25 subjects are required when *α* = 0.000002, to achieve a stable statistical power [28–30]. Considering a 20% attrition rate and possible excessive head motions occur in the fMRI scanning, we plan to recruit 30 subjects in each group.

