### Interventions

Each type of acupuncture treatment will include 12 sessions of 30-min duration over 4 weeks (3 sessions per week). The date of each patient’s treatment will be recorded, and the number of treatments received by each patient at intervention phase I and intervention phase II will be counted for monitoring adherence. The licensed acupuncturists with more than 5 years of experience with acupuncture will be trained for a standard intervention procedure before this study. Patients will be given paracetamol sustained-release tablets (Tylenol; Shanghai Johnson Pharmaceutical Co., Ltd.) as a rescue medication when they have excessive pain, and the administration of rescue medication will be recorded in detail.

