### Neuroimaging data evaluation

Many functional systems of the brain are involved in pain modulation, such as descending pain, affective, and cognitive processing systems. Resting state fMRI data will be measured to identify the neurological mechanisms of the specific and nonspecific effects of acupuncture. Functional MRI scanning will be carried out using a Siemens 3.0 Tesla scanner (Skyra, Siemens, Erlangen, Germany) equipped with a standard head coil at the Beijing Hospital of Traditional Chinese Medicine Affiliated to Capital Medical University. During the resting state fMRI acquisition, patients will be in a supine position with their eyes closed and be instructed to remain awake and avoid thinking. The resting state fMRI data will be obtained using a gradient echo planar imaging (EPI) sequence with the following parameters: whole brain, repetition time (TR) = 2000 ms, echo time (TE) = 30 ms, field of view (FOV) = 224 mm × 224 mm, flip angle (FA) = 90°, slice thickness/gap = 3.5/0.6 mm, voxel size =3.5 mm × 3.5 mm × 3.5 mm, axial slices = 32, in-plane resolution = 64 × 64, and 240 volumes. Foam pads will be used to minimize head motion and earplugs will be used to reduce noise interference. The fMRI scans will be performed at baseline and the end of 4-week treatment in each phase (Fig. 3).

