### Statistical analysis

#### Clinical data analysis

The continuous variables will be described as the mean (standard deviation) or the median. The categorical variables will be described as the percentage. The comparisons between the two groups will be analyzed by independent sample *t* test, Wilcoxon rank-sum, or *χ*^2^ test in demographic, psychological factors and other indicators. The comparison between the acupuncture and sham acupuncture will be analyzed using general liner model. Intention-to-treat analysis (ITT) will be mainly used to evaluate the efficacy of acupuncture. ITT analysis will be performed to analyze all randomized data, and last observation carried forward (LOCF) will be adopted to impute the missing values. Per protocol analysis will be used and per protocol population will include patients who complete at least 10-session acupuncture during each phase and finish 4 fMRI scans. The specific effect of acupuncture will be calculated by subtracting the effect in sham acupuncture from the acupuncture. The nonspecific effect of acupuncture will be calculated by subtracting the pre-acupuncture from the post-acupuncture in sham acupuncture phase. The data will be statistically analyzed by SPSS software.

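### Excluding patients who miss more than 6 of 24 sessions adds nothing to the per-protocol screen and can hand obtainable end-of-phase outcomes to LOCF in the main ITT analysis

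*Protocol article*

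**What the plan says.** The second list under Exclusion criteria applies while the trial is running: "patients with KOA who meet the following criteria will be excluded from the study". Item (3) is "missing more than 6 of 24 acupuncture treatment sessions". It stands beside withdrawal of consent and, as item (4), "occurrence of a serious adverse event that the doctors consider should lead to termination of trial participation".

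Under Clinical data analysis, "Intention-to-treat analysis (ITT) will be mainly used to evaluate the efficacy of acupuncture", and "ITT analysis will be performed to analyze all randomized data, and last observation carried forward (LOCF) will be adopted to impute the missing values". The per-protocol set has its own adherence rule: at least 10 sessions in each phase, plus all four fMRI scans. The Interventions section already provides that "the number of treatments received by each patient at intervention phase I and intervention phase II will be counted for monitoring adherence".

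The primary outcome (Clinical outcomes evaluation) is the NRS change after 4 weeks of intervention. The specific effect is the acupuncture effect minus the sham effect, and the nonspecific effect is post minus pre in the sham phase. Scans follow the same pattern: "The fMRI scans will be performed at baseline and the end of 4-week treatment in each phase".

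**The concern.** Two adherence rules stand side by side. One defines an analysis set and works phase by phase. The other pools both phases and removes the patient from the study. Given its neighbours in the list, the natural reading of item (3) is that participation ends, so NRS, SF-MPQ, WOMAC and fMRI at the end of the current phase, and of any later phase, may not be collected. Nothing in the article says that data already collected are deleted.

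The main analysis keeps every randomized patient, so the rule does not shrink the ITT set. Instead it turns outcomes that might have been observed into LOCF values. If LOCF carries the phase's pre-treatment score, the change for that phase becomes zero, and both quantities in the first objective, the specific and the nonspecific effect, shrink when pooled. Unless misses are strongly clustered within patients, most triggers fall in phase II. That phase is sham in group A and acupuncture in group B, so the two sequences are distorted in opposite directions.

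**Working it through.** **Inputs from the article.** 12 sessions per phase, 3 per week for 4 weeks, two phases: 2 × 3 × 4 = 24, which reproduces the stated total. Exclusion needs 7 or more misses. Per protocol allows at most 2 misses in each phase. There are 60 patients, hence 120 phase endpoints.

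**Assumed, because the article gives no figure.** Miss probability per session m = 10%, 15% or 20%. Within-patient correlation of misses (ICC) 0, 0.1 or 0.5, using a beta-binomial model when it is not 0. Share r of excluded patients who would otherwise have been assessed: 1, 0.5 or 0.25. True NRS changes of 3 (acupuncture) and 2 (sham). The phase baseline is carried forward.

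**Step 1: overlap of the two rules.** Of all pairs (i, j) of phase I and phase II misses with 0 ≤ i, j ≤ 12, 141 have i + j > 6. The smallest value of max(i, j) among them is 4, and none has both i and j ≤ 2. Every patient caught by item (3) has therefore completed 8 or fewer sessions in some phase and already fails the 10-session rule.

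**Step 2: when the rule fires.** For independent misses, the seventh miss falls at session s with probability C(s−1, 6) m^7 (1−m)^(s−7). In the last treatment week (sessions 22–24) the endpoint may still be collected, so the phase II endpoint is counted at risk only if s ≤ 21 (probability f2). The phase I endpoint is at risk only if s ≤ 9 (probability f1).

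**Step 3: effect on the estimate.**
- Endpoints lost to the rule, of 120: 60r(f1 + f2).
- Group A difference: 3(1 − r·f1) − 2(1 − r·f2).
- Group B difference: 3(1 − r·f2) − 2(1 − r·f1).
- Average of the two: 1 − r(f1 + f2)/2.

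| ICC | m | Rule fires at all | f2 | f1 | Endpoints lost, r = 1 | Pooled difference, r = 1 / 0.5 / 0.25 |
|---|---|---|---|---|---|---|
| 0 | 10% | 0.7% | 0.0033 | 0.0000 | 0.2 | 1.00 / 1.00 / 1.00 |
| 0 | 15% | 5.7% | 0.0287 | 0.00005 | 1.7 | 0.99 / 0.99 / 1.00 |
| 0 | 20% | 18.9% | 0.1085 | 0.0003 | 6.5 | 0.95 / 0.97 / 0.99 |
| 0.1 | 10% | 8.6% | 0.0618 | 0.0014 | 3.8 | 0.97 / 0.98 / 0.99 |
| 0.1 | 15% | 17.2% | 0.1287 | 0.0040 | 8.0 | 0.93 / 0.97 / 0.98 |
| 0.1 | 20% | 28.0% | 0.2184 | 0.0089 | 13.6 | 0.89 / 0.94 / 0.97 |
| 0.5 | 10% | 13.6% | 0.1239 | 0.0444 | 10.1 | 0.92 / 0.96 / 0.98 |
| 0.5 | 15% | 20.5% | 0.1880 | 0.0718 | 15.6 | 0.87 / 0.94 / 0.97 |
| 0.5 | 20% | 27.3% | 0.2527 | 0.1026 | 21.3 | 0.82 / 0.91 / 0.96 |

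**Reading the table.**
- With independent misses, 56%, 50% and 43% of triggers (m = 10%, 15%, 20%) fall in the last treatment week and are not counted as losses.
- Of the triggers before that week, 81–87% are in phase II at ICC 0.1, and 37–41% at ICC 0.5.
- Worked row, ICC 0.1, m = 10%, r = 1. Group A: 3(1 − 0.0014) − 2(1 − 0.0618) = 1.12. Group B: 3(1 − 0.0618) − 2(1 − 0.0014) = 0.82. Average 0.97.
- The pooled sham change shrinks by the same proportion: 2 × [1 − (0.0618 + 0.0014)/2] = 1.94.
- If a mid-phase value halfway to the endpoint is carried, every shift halves.

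**Plausibility of m.** With independent misses, the chance of failing the 10-per-phase rule is 21%, 46% and 69% at m = 10%, 15% and 20%. The Sample size section plans on 20% attrition. That is a different quantity, but it makes 10% the most believable of the independent cases.

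**The case against.** The best defence is that item (3) governs participation while the 10-session rule defines an analysis set. A looser stopping rule next to a stricter per-protocol rule is ordinary, and the two do not conflict. That is right, and redundancy alone would not be worth raising. The issue is that the rule has a possible cost in the main analysis and no offsetting gain in the per-protocol one.

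A second point is that the article never says excluded patients go unassessed, and a condensed article may leave that to the full protocol. This stands as a limit on certainty: the harm is something the rule can do. But the criterion itself is explicit, and its wording and neighbours point to the end of participation.

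Third, the sizes are assumed and the larger ones lean on patients who have mostly stopped coming. At ICC 0.5 and m = 10%, patients who trigger the rule miss on average 14.2 of 24 sessions, and 61% miss 12 or more. For them r = 1 is not believable; at r = 0.25 the pooled difference is 0.98. The most plausible independent case shows essentially no effect. The carried value is also unknown, since the assessment schedule is in a figure not available here. All of this stands, and it keeps the size at negligible to modest.

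Finally, item (1) of the same list, on unpermitted analgesics or additional treatment, could cause the same loss and is more closely tied to pain. That is true. It argues for giving that item the same treatment, not for keeping item (3).

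**Conclusion.** The concern holds. The redundancy is exact arithmetic and needs no assumption. The effect on the ITT estimate depends on reading exclusion as the end of outcome assessment, and on assumed miss rates, clustering, recovery and carried value. At a 10% miss rate the rule costs between 0.05 of 120 endpoints (independent misses, r = 0.25) and 10.1 (ICC 0.5, r = 1), and the pooled difference of 1.00 falls to between 1.00 and 0.92. The more credible combinations lie at 0.97 or above. Shifts within a sequence are larger and opposite in sign, which the pooled figure hides. This would rarely change a conclusion, but it is avoidable missing data in the main analysis of a 60-patient trial, and the change is worth making because it is cheap.

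**What to change.** Delete item (3) from the on-study list under Exclusion criteria. Add in its place: *Patients who miss sessions remain in the study. If they agree, they have the end-of-phase NRS, SF-MPQ, WOMAC and fMRI, enter the other phase, and are analysed by ITT with their observed values.* Leave the per-protocol rule of at least 10 sessions in each phase unchanged; by Step 1 its membership is not affected.

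The cost is one deletion and one short addition. Sessions are already counted per phase, so nothing new has to be recorded. A few poor attenders must still be assessed and scanned, and some will decline. Those who have stopped attending altogether would mostly be lost with or without the rule.

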### Randomization and blinding

Eligible patients will be randomly assigned to one of two groups in a 1:1 ratio. The randomization sequence and grouping will be generated and stored by a specific statistician who will not participate directly in this study using the software SAS 9.3 (SAS Institute, Cary, NC, USA). Acupuncturists cannot be blinded to treatment allocation, and they will not be allowed to discuss with patients the type of intervention. The outcome evaluators, fMRI scanners, statisticians, and all patients will be blinded to group assignment until completion of the study.

### Sample size

Since this is a pilot study, a formal sample size calculation is not performed [27]. According to fMRI studies, a sample size of 20 subjects are sufficient to detect a significant difference with a type I error of 5%, and about 25 subjects are required when *α* = 0.000002, to achieve a stable statistical power [28–30]. Considering a 20% attrition rate and possible excessive head motions occur in the fMRI scanning, we plan to recruit 30 subjects in each group.

### Interventions

Each type of acupuncture treatment will include 12 sessions of 30-min duration over 4 weeks (3 sessions per week). The date of each patient’s treatment will be recorded, and the number of treatments received by each patient at intervention phase I and intervention phase II will be counted for monitoring adherence. The licensed acupuncturists with more than 5 years of experience with acupuncture will be trained for a standard intervention procedure before this study. Patients will be given paracetamol sustained-release tablets (Tylenol; Shanghai Johnson Pharmaceutical Co., Ltd.) as a rescue medication when they have excessive pain, and the administration of rescue medication will be recorded in detail.

#### Acupuncture treatment

The acupoints for the acupuncture intervention will include Dubi (ST 35), Neixiyan (EX-LE4), Ququan (LR8), Xiyangguan (GB33), Xuehai (SP10), Sanyinjiao (SP6), Taixi (KI3) and an ashi point (the point where the patient feels most pain). An adhesive pad will be placed on the skin above the acupoints according to WHO Standard Acupuncture Locations, and then a single-use sterile needle (0.25 × 40 mm or 0.25 × 25 mm, Hwato, Suzhou, China) will be used to penetrate into the skin 5–20 mm through the adhesive pad (Fig. 2). Acupuncturists will manually stimulate the needles to achieve de qi (mainly including the sensations of numbness, distention, soreness and heaviness), and then the needles will be left in place for 30 min. Table 1 and Fig. 2 show the location of acupoints for acupuncture.

**Fig. 2 Fig2:**
[figure not shown]
The picture of acupuncture and sham acupuncture. **a** Location of acupoints and non-acupoints. Red circles: Acupoints used in acupuncture group. Blue circles: Non-acupoints used in sham acupuncture group. **b** The diagrammatize of acupuncture and sham acupuncture. Abbreviation: ST35 Dubi, EX-LE4 Neixiyan, LR8 Ququan, GB33 Xiyangguan, SP10 Xuehai, SP6 Sanyinjiao, KI3 Taixi. NA, non-acupoint

**Table 1 Tab1:** Locations of acupoints for acupuncture

Acupoints	Locations
Dubi (ST 35)	On the anterior aspect of the knee, in the depression lateral to the patellar Ligament
Neixiyan (EX-LE4)	On the anterior aspect of the knee, in the depression medial to the patellar Ligament
Ququan (LR8)	On the medial aspect of the knee, in the depression medial to the tendons of the semitendinosus and the semimembranosus muscles, at the medial end of the popliteal crease
Xiyangguan (GB33)	On the lateral aspect of the knee, in the depression between the biceps femoris tendon and the iliotibial band, posterior and proximal to the lateral epicondyle of the femur
Xuehai (SP10)	On the anteromedial aspect of the thigh, on the bulge of the vastus medialis muscle, 2 cun superior to the medial end of the base of the patella
Sanyinjiao (SP6)	On the tibial aspect of the leg, posterior to the medial border of the tibia, 3 cun superior to the prominence of the medial malleolus
Taixi (KI3)	On the posteromedial aspect of the ankle, in the depression between the prominence of the medial malleolus and the calcaneal tendon

^a^1 cun (≈ 20 mm) is defined as the width of the interphalangeal joint of patient’s thumb

#### Sham acupuncture treatment

Non-acupoints will be used for the sham acupuncture intervention, and the locations of the non-acupoints are shown in Table 2 and Fig. 2. An adhesive pad will be placed on the skin of non-acupoints, and then a blunt single-use sterile needle (0.25 × 40 mm or 0.25 × 25 mm, Hwato, Suzhou, China.) will be used to penetrate into the adhesive pad, but not penetrate into the skin (Fig. 2) [31, 32]. The needles will be left in place for 30 min. Table 2 and Fig. 2 show the location of non-acupoints for sham acupuncture.

**Table 2 Tab2:** Locations of non-acupoints for sham acupuncture

Non-acupoints	Locations
Non-acupoint 1	On the anterior aspect of the thigh, 6 cun above the upper edge of the patella (between the spleen and stomach meridian)
Non-acupoint 2	On the anterior aspect of the thigh, 5 cun above the upper edge of the patella (between the spleen and stomach meridian)
Non-acupoint 3	On the anterior aspect of the thigh, 4 cun above the upper edge of the patella (between the spleen and stomach meridian)
Non-acupoint 4	In the middle of GB34 and ST36 (between the gallbladder and bladder meridian)
Non-acupoint 5	3 cun below GB34 (between the gallbladder and bladder meridian)
Non-acupoint 6	2 cun above the medial malleolus (between the liver and spleen meridian)
Non-acupoint 7	In the middle of GB40 and ST41 (between the gallbladder and bladder meridian)

^a^1 cun (≈ 20 mm) is defined as the width of the interphalangeal joint of patient’s thumb

### Clinical outcomes evaluation

The pain-related scales will be used to evaluate the magnitude of acupuncture’s specific and nonspecific effects in treating KOA. The primary outcome will be the change of pain on the Numerical Rating Scale (NRS) after 4 weeks of intervention. And the minimal clinically important improvement (MCII) will be defined as at least 2-point reduction on the NRS, and patients who attain the MCII will be defined as responders [9, 33]. The secondary clinical outcomes will include the change of short-form of the McGill Pain Questionnaire (SF-MPQ) and Western Ontario and McMaster Universities Osteoarthritis Index (WOMAC). The SF-MPQ, which includes sensation and affection of pain [34], will be used to assess the pain quality. The WOMAC consists of three subscales with five-point Likert scale: pain, stiffness, and physical function [35]. Adverse events and blinding assessment during the study will be recorded (Fig. 3).

**Fig. 3 Fig3:**
[figure not shown]
Schedule of intervention and assessments. NRS, Numerical Rating Scale; WOMAC, Western Ontario and McMaster Universities Osteoarthritis Index; SF-MPQ, short form McGill pain questionnaire; BFP, Big Five Personality; MAAS, Mindful Attention Awareness Scale; TMMS, Trait Meta-Mood Scale; SETS, Stanford Expectations of Treatment Scale; fMRI, functional magnetic resonance imaging

### Neuroimaging data evaluation

Many functional systems of the brain are involved in pain modulation, such as descending pain, affective, and cognitive processing systems. Resting state fMRI data will be measured to identify the neurological mechanisms of the specific and nonspecific effects of acupuncture. Functional MRI scanning will be carried out using a Siemens 3.0 Tesla scanner (Skyra, Siemens, Erlangen, Germany) equipped with a standard head coil at the Beijing Hospital of Traditional Chinese Medicine Affiliated to Capital Medical University. During the resting state fMRI acquisition, patients will be in a supine position with their eyes closed and be instructed to remain awake and avoid thinking. The resting state fMRI data will be obtained using a gradient echo planar imaging (EPI) sequence with the following parameters: whole brain, repetition time (TR) = 2000 ms, echo time (TE) = 30 ms, field of view (FOV) = 224 mm × 224 mm, flip angle (FA) = 90°, slice thickness/gap = 3.5/0.6 mm, voxel size =3.5 mm × 3.5 mm × 3.5 mm, axial slices = 32, in-plane resolution = 64 × 64, and 240 volumes. Foam pads will be used to minimize head motion and earplugs will be used to reduce noise interference. The fMRI scans will be performed at baseline and the end of 4-week treatment in each phase (Fig. 3).

### Psychological factors evaluation

Psychological factors assessment will include the Mindful Attention Awareness Scale (MAAS), Trait Meta-Mood Scale (TMMS), Big Five Personality (BFP), and Stanford Expectations of Treatment Scale (SETS). MAAS will be used to assess the variations in awareness and attention to present experience [36, 37]. TMMS will be used to assess the capacity to identify emotional states and regulate them [38]. BFP is a widely used personality factors scale, which includes openness, conscientiousness, extraversion, agreeableness, and neuroticism [39, 40]. SETS is a suitable scale to assess individual expectation for upcoming interventions [41]. These psychological factors are relatively stable and not easily modifiable, so they will be only assessed at baseline (Fig. 3). Correlation analyses will be performed to determine the relationships among the brain activity changes, psychological factors, and symptom improvement (Fig. 4).

**Fig. 4 Fig4:**
[figure not shown]
Statistical analysis flow

### Oxytocin and genetics evaluation

Although valid scales will be adopted to assess the individual psychological factors, these scales are subjective. Oxytocin is a neurotransmitter associated with psychological factors, and it could be used as an objective indicator for further estimating how psychological factors affect the specific and nonspecific effects of acupuncture [42]. Neurophysiological study indicated that genetic variations in neurotransmitter pathways mediating placebo effects provided the possibility of identifying placebo responders through genetic screening [43]. Based on recent studies, catechol-o-methyltransferase (COMT) and opioid receptor (OPRM1) participated in mediating the regulation of psychological process and pain process [44–47]. These genes will be selected as candidate genes for objectively assessing and predicting the specific and nonspecific effects of acupuncture, estimating correlations among gene polymorphisms, psychological factors, and brain activity.

At baseline, KOA patients will be asked to fasting at least 8 h prior to the sample collection and blood will be obtained in the morning from a vein in upper arm. The blood samples will be centrifuged immediately. Then, plasma and blood cells will be separated into two refrigerating tubes and stored at − 80 °C. Sequent, samples will be sent to technical laboratory to be processed by standard means. This study involves collecting biological specimens for storage. On the consent form, patients will be asked if they agree to use of their data. Patients will also be asked for permission for the research team to share relevant data with people from the universities taking part in the research.

